**Description of Research**

This double-blind, controlled and randomized study will be carried out in a hospital where policy dictates that all women should receive 10 IU of prophylactic oxytocin in the third stage of labor. Furthermore, the majority of women who give birth in the study hospital already have an IV line in place. The study objective will be to evaluate the impact of route of administration of 10 IU oxytocin on postpartum bleeding. Eligible women who provide informed consent and give birth vaginally will be randomized to receive either:

- 10 IU oxytocin via IV infusion
- 10 IU oxytocin via IM injection

Oxytocin 10 IU will be administered either by IV infusion or IM according to randomization assignment as soon as possible after delivery of the baby. The IV infusion will be done by placing 10 IU of oxytocin in a bag of saline solution of 500 cc and then administered over 40 minutes (eg, 12cc/min or 240drops/min). All study participants will receive oxytocin by IV infusion or by IM injection, based on randomized allocation, and the corresponding placebo by the non-assigned route.

To avoid any potential bias that knowledge of the route of administration of oxytocin may have in the quantification of blood loss, study staff members and participants will not know the assignment of the route of administration of the active drug. Since all delivering women in the study hospital routinely have an IV line in place, all study participants will receive oxytocin by either IV infusion or IM injection, based on randomization assignment, in addition to placebo by the non-assigned route. Blood loss will be measured in a calibrated container for 1 hour. If a woman experiences excessive bleeding or PPH, she will receive treatment according to standard of care at the study site.

Independent of the diagnosis of PPH, consenting women who have a vaginal delivery will have their postpartum blood loss measured using a standardized receptacle, in addition to other indicators and outcomes recorded during the immediate postpartum period to assess the relationship between shock index and PPH outcomes. Blood loss will be measured for 1 hour, and if PPH diagnosed, measurement will continue until cessation of active bleeding. Pulse and blood pressure will be measured at pre-defined intervals (15, 30, 45, and 60 minutes) in order to document hemodynamic changes that occur during the immediate postpartum period.

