***Informed Consent and Pre-delivery Procedures***

Informed consent will be obtained by trained study personnel after women have been admitted to the hospital and upon arrival at the labor ward. If study personnel feel that the woman is too far advanced in her labor to give appropriate informed consent, she will not be eligible for enrollment. Women who decline to participate in the study will be given full medical care according to standard practice in the facility. Women who wish to participate will be asked to read and sign the informed consent form. If the woman is unable to read, the form will be read and explained to her, and her consent will be indicated by a mark, such as the woman’s thumbprint. If at any point during her participation in the study the woman indicates that she no longer wishes to continue, she will be withdrawn from further data collection.

Background characteristics and baseline data will be obtained and documented on Form 1. Pre-delivery hemoglobin will be measured and recorded for all women, using a Hemocue® Hemoglobin machine + cuvette (HemoCue, Ängelholm, Sweden).

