Post-delivery hemoglobin using a Hemocue® Hemoglobin machine + cuvette will be taken at least 24 after delivery and before the woman leaves the facility. If the woman has received IV fluids, hemoglobin will be measured at least 12 hours after removal of the IV prior to discharge.

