***Analysis and Dissemination of Results***

Bivariate analyses will be conducted, stratified by study arm. Unadjusted and adjusted logistic regression will be conducted respectively for categorical and continuous dependent variables.

To compare the two study arms (oxytocin IM vs. oxytocin infusion), the main analyses will include:

- Mean postpartum blood loss (primary outcome)
- % of women with blood loss ≥500 ml (primary outcome)
- Median postpartum blood loss and interquartile range
- % of women with blood loss ≥1000 ml,
- Mean change in Hb measured pre- to post-delivery
- % of women with postpartum Hb drops of 2 g/dl or greater
- % of women with prolonged third stage of labor
- % of women who received additional oxytocics or other interventions to manage bleeding
- % of women who experienced side effects

We will register use of any other AMTSL components, such as controlled cord traction, uterine massage, etc. that are used.

In order to assess the relationship between shock index and severity of bleeding, we will correlate shock index values, heart rate, and blood pressure measures to blood loss levels that will be recorded at 15, 30, 45, and 60 minutes following delivery. Absolute values and measured changes in these values during the first hour following delivery will be analyzed. We will also explore associations between these clinical signs/symptoms with other PPH outcomes, including provision of additional interventions to control bleeding, blood transfusion, and other severe outcomes.

Data will be owned by Gynuity Health Projects. The principal investigators and study coordinators will work together to analyze the results of the study and prepare at least one manuscript for submission to one or more relevant peer-reviewed journals. In addition, members of the study team will present the results of the study at conferences and meetings where appropriate. All principal investigators will be named along with key Gynuity staff as authors of any publications or presentations describing results from the study.

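### The hemoglobin comparison is listed as a raw pre-to-post change, with pre-delivery hemoglobin not named as a covariate, so it gives up precision; the sampling-time rules also need reconciling

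*Protocol*

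**What the plan says.** Research question 2 asks whether the pre- to post-delivery difference in hemoglobin is smaller with IV infusion than with IM injection. Change in hemoglobin is a secondary outcome.

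- **Baseline** (Informed Consent and Pre-delivery Procedures): "Pre-delivery hemoglobin will be measured and recorded for all women".
- **Comparison** (Analysis and Dissemination of Results): the main between-arm analyses include "Mean change in Hb measured pre- to post-delivery" and the percentage "of women with postpartum Hb drops of 2 g/dl or greater".
- **Regression** (same section): "Unadjusted and adjusted logistic regression will be conducted respectively for categorical and continuous dependent variables". No covariates are listed there. The only adjustment variables named elsewhere are the other components of active management (Background).
- **Sampling time, general rule** (Intervention): the post-delivery sample "will be taken at least 24 after delivery and before the woman leaves the facility". The unit after 24 is missing.
- **Sampling time, conditional rule** (next sentence): "If the woman has received IV fluids, hemoglobin will be measured at least 12 hours after removal of the IV prior to discharge".
- **Who gets an infusion** (Description of Research): each woman receives oxytocin by her assigned route "and the corresponding placebo by the non-assigned route". The IV bag is 500 cc, given over 40 minutes.

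**The concern.** A change score fixes the weight on the baseline value at exactly one. Regression lets the data choose that weight and so uses the baseline at least as well. When the baseline is already collected in all women, a raw change as the stated comparison discards information that costs nothing to use. At stake is the width of the confidence interval that answers research question 2.

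On timing, a rule written as an exception applies to the whole trial, because both arms receive an infusion. If staff read the two sentences differently, the earliest permitted sampling time varies between women for reasons unrelated to blood loss, which adds noise to the same outcome.

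**Working it through.** **Inputs.** The Protocol gives no hemoglobin SD, no pre-post correlation and no power figure for this outcome, so there is no stated hemoglobin figure to reproduce. Its sample size rests on blood loss and PPH and has no bearing here. I therefore assume r, the pre-post correlation within arm, from 0.5 to 0.8, and k, the ratio of post- to pre-delivery SD, from 1.0 to 1.2.

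**Formulas**, in units of the pre-delivery variance:

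- Change score: 1 + k² − 2rk
- Baseline-adjusted: k²(1 − r²)
- Difference between them: (1 − rk)², which is never negative. Adjustment is therefore never less precise asymptotically, and the gain vanishes only when rk = 1.

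**Equal SDs (k = 1).** The ratio of adjusted to change-score variance is (1 − r²) / [2(1 − r)] = (1 + r)/2.

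- r = 0.5: 0.75 / 1.00 = 0.75. The change score needs 1/0.75 − 1 = 33% more women for equal precision, and its interval is 15% wider (√(1/0.75) = 1.155).
- r = 0.8: 0.36 / 0.40 = 0.90. The corresponding figures are 11% more women and an interval 5% wider (√(1/0.90) = 1.054).

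**Wider post-delivery SD (k = 1.2).**

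- r = 0.5: 1.44 × 0.75 = 1.08; 1 + 1.44 − 1.20 = 1.24; ratio 0.87.
- r = 0.8: 1.44 × 0.36 = 0.5184; 1 + 1.44 − 1.92 = 0.52; ratio 0.997.

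| k | r = 0.5 | r = 0.7 | r = 0.8 |
|---|---|---|---|
| 1.0 | 0.75 | 0.85 | 0.90 |
| 1.1 | 0.82 | 0.92 | 0.97 |
| 1.2 | 0.87 | 0.97 | 0.997 |

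**Does the planned regression already deliver this?** Not as written. The sentence assigns logistic regression to continuous outcomes, which cannot be carried out, and names no covariate. It does not rule out baseline adjustment either.

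**Timing.** The infusion starts as soon as possible after delivery and runs 40 minutes.

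- If the conditional rule replaces the general one, a woman whose IV is removed when the infusion ends could be sampled from about 40 min + 12 h = 12 h 40 min. The general rule would then apply to nobody.
- If it adds to the general rule, the earliest time is 24 (presumably hours), or 12 hours after IV removal if that is later.

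Discharge is the only upper limit under either reading. The Intervention section requires the exact time of each pulse and blood pressure reading. It states no such requirement for the hemoglobin sample, and neither does the Study Documentation section.

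**The case against.** **Covariates belong in the SAP, and a change score is valid.** Both statements are true. The missing covariate list is not itself a fault, the change score is unbiased under randomization, and it matches the wording of research question 2. But the Protocol does name a method for this comparison, and a better one is available from data it already collects. The adjusted estimate answers the same question: regressing post-delivery hemoglobin or the change on arm and baseline gives the same arm coefficient.

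**The gain may be negligible.** This stands in part. At k = 1.2 and r = 0.8 almost nothing is gained. Nor is anyone recruited because of the hemoglobin estimator, so the 11% to 33% is only a way of expressing precision.

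**The two timing rules do not contradict each other.** This stands. Both are minimum times and one sample can satisfy both, so they are unreconciled rather than conflicting. They apply equally to both blinded arms. A reader might infer that women who bleed keep the IV longer and are sampled later, but the Protocol does not say so.

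**Transfused women.** A reader might infer that the plan takes their hemoglobin at face value and so hides the worst bleeders. The first part rests on silence, on a matter a SAP commonly covers. The second is contradicted by the Protocol, which analyses blood loss of 1000 ml or more and additional interventions to manage bleeding, and lists transfusion within a secondary outcome. Any masking would be confined to the hemoglobin measures. The shift in the mean difference is the difference in transfusion rates times the hemoglobin rise. With assumed rates it runs from (0.01 − 0.005) × 1 = 0.005 g/dl to (0.05 − 0.02) × 3 = 0.09 g/dl.

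**Conclusion.** The point holds as a free improvement to a secondary outcome, not as a correction of bias. Baseline adjustment reduces the variance of the arm difference to 0.75 to 0.90 of the change-score variance if the two SDs are equal and r lies between 0.5 and 0.8. If the post-delivery SD is 1.2 times the pre-delivery SD, the ratio is 0.87 to nearly 1.00. Both r and the SD ratio are assumptions. That adjustment is never less precise asymptotically does not depend on them.

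The timing wording is a lesser point: an ambiguity that affects every participant, in both arms alike. The documents support no finding that transfused women are mishandled or that severe bleeding is concealed.

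**What to change.** 1. State that the arm difference in hemoglobin is estimated by linear regression of post-delivery hemoglobin (or of the change) on arm, with pre-delivery hemoglobin as covariate. Keep the raw mean change by arm as a descriptive summary.
2. Reconcile the two sampling-time sentences in the Intervention section into one statement for both arms. Supply the missing unit, and say whether the rule tied to IV removal adds to or replaces the general one. Record the time of the post-delivery sample.
3. Optional: a sensitivity analysis of the 2 g/dl outcome that counts transfused women as events. The outcome definition need not change.

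Item 1 costs a sentence of analysis text and uses data already planned. Item 2 is a clarification of study procedure and, if the form does not already capture the sampling time, one added field. Item 3 is one extra table row.

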# Is shock index a potential useful indicator for evaluating the severity of postpartum bleeding during the first hour postpartum and initating clincial intervention for PPH management?

**Outcome Measures**

Primary outcome measures:

- Mean blood loss (ml)
- Proportion of women who bleed  500 ml

Secondary outcome measures:

- Proportion of women who bleed  1000 ml
- Change in hemoglobin from pre-delivery to postpartum
- Time to placental delivery
- Administration of additional oxytocin, other uterotonics, or other interventions such as blood transfusion and hysterectomy
- Side effects 1 hour postpartum
- Measurements of blood pressure and pulse during the first hour postpartum.

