**Explanation of Sample Size**

The primary outcomes of the study are (1) mean blood loss and (2) the proportion of women with PPH (defined as ≥500 ml).

This study is designed to detect a 50 ml difference in mean blood loss after provision of oxytocin prophylaxis via IV infusion and IM injection. In the published literature, a 50 ml difference has been shown to translate to approximately a 50% reduction in PPH rates (≥500 ml) . Based on the assumption that oxytocin prophylaxis IV will yield a mean blood loss of 275 (SD175)we estimate that a total of 257 women would be required in this superiority trial to detect a 50 ml difference in mean blood loss between the two groups with 80% power at a significance level of 0.05.

A prior study of PPH conducted at Hospital Vida had documented a rate of blood loss ≥500 ml of 18%, among women who received prophylactic oxytocin (10 IU) in the third stage of labor and with blood loss objectively assessed using a calibrated receptacle. Based on the assumption that oxytocin prophylaxis IV will yield a clinically meaningful reduction of at least 50% in the proportion of women with blood loss ≥500 ml , we calculate that a total of 442 women (vaginal deliveries) (221 per group) are required in this superiority trial to compare a 18% PPH rate following IM injection and a 9% PPH rate following IV infusion with 80% power at a significance level of 0.05. The sample size will be increased by 10% to account for any loss to follow up or missing blood loss readings for assessment of both primary outcomes. Thus, **a total sample size of 486 (243 per arm) is required** for the study in Ecuador. This sample size will be sufficient to detect a 50 ml mean difference in blood loss between study groups.

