***Study Documentation***

*Admission*. This form will document basic demographic characteristics and medical and obstetrical history to assess women’s eligibility for study participation. It will also document that each woman has signed the informed consent form. This form will be completed for all consenting women.

*Randomization/Delivery*. This form will document randomization number and relevant information during and post delivery, including time of delivery and events or interventions during the third stage of labor, especially with regard to administration of uterotonic agents as well as other components of active management. This form will also record any diagnosis of PPH. The form will be completed for all consenting women.

*Follow-up.* This form will be used to record information on side effects, adverse events, or problems following delivery at follow-up prior to discharge from the hospital. Post-delivery hemoglobin will be measured and recorded at this time.

*Severe Adverse Events (SAEs) Form*. This form will be used to document any SAEs as defined below. It should be completed by the principal investigator and forwarded to Gynuity Health Projects staff within 24 hours of his/her awareness of the event.

A serious adverse event is defined as one causing:

- Prolonged hospitalization;
- Permanent or serious disability;
- Additional threat to life; or
- Death.

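### Time to placental delivery is a declared secondary outcome, but the listed arm comparisons include only a percentage with a 'prolonged' third stage, without a cut-off

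*Protocol*

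**What the plan says.** Under Outcome Measures, the secondary outcomes include "Time to placental delivery", which is a duration.

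Under Analysis and Dissemination of Results, the arm comparisons are introduced with "the main analyses will include". The only item there that concerns the third stage is the percentage "of women with prolonged third stage of labor". The protocol nowhere says how many minutes count as prolonged.

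The same list handles hemoglobin in two ways: "Mean change in Hb measured pre- to post-delivery", and the percentage "of women with postpartum Hb drops of 2 g/dl or greater". Blood loss likewise appears as a mean, as a median with interquartile range, and as proportions at or above 500 ml and 1000 ml.

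The regression sentence reads "Unadjusted and adjusted logistic regression will be conducted respectively for categorical and continuous dependent variables". It names no method suited to a duration.

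Under Study Documentation, the Randomization/Delivery form covers relevant information "including time of delivery and events or interventions during the third stage of labor". The time of placental delivery is not named.

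**The concern.** A reader who looks up how the declared duration will be compared finds a different quantity, whose definition is missing. Two consequences follow.

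First, 'prolonged' can mean many things. As the text stands, a cut-off chosen after the data have been seen would comply with the protocol.

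Second, the Background section says that onset of action differs between intravenous and intramuscular oxytocin, so an effect of route on third-stage duration is a reasonable question. If the effect is a modest shift across all women, a proportion beyond a cut-off is a weaker way to detect it than the times themselves. A null result on the proportion could then be read as no effect on duration.

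**Working it through.** **1. The continuous outcomes side by side**, from the list of arm comparisons:

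| Outcome | Continuous summary listed | Binary version listed | Cut-off stated |
|---|---|---|---|
| Blood loss | Mean; median and IQR | Two proportions | 500 ml; 1000 ml |
| Hemoglobin change | Mean change | Proportion with a drop | 2 g/dl |
| Third-stage duration | None | Proportion prolonged | None |

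Third-stage duration is the only one with no continuous summary and the only one whose binary version has no threshold.

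**2. Figures in the plan.** The protocol states no figure for this outcome. The one number borrowed below is 221 women per group, from Explanation of Sample Size, which compares "18% PPH rate following IM injection and a 9% PPH rate following IV infusion" at 80% power and a 0.05 level. Sidedness is not stated; two-sided is assumed. As a background check, the pooled-variance formula gives

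n = [1.960·√(2·0.135·0.865) + 0.842·√(0.18·0.82 + 0.09·0.91)]² / 0.09² = (0.947 + 0.403)² / 0.0081 = 225.1,

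so 226 per group, or 452 in total, 2.3% above the stated 442. The arcsine formula, with h = 2(arcsin√0.18 − arcsin√0.09) = 0.2669, gives 2·(1.960 + 0.842)² / h² = 220.3, so 221. The plan's figure is reproduced.

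**3. Information kept by a percentage.** Assume that the times are normal, or normal after taking logs, and that route shifts them. If a fraction p of women lies beyond the cut-off, z is the normal quantile at 1 − p and φ is the normal density, then the efficiency of the percentage relative to a comparison of means on that scale is

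φ(z)² / [p(1 − p)].

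| p prolonged | z | φ(z) | Information kept |
|---|---|---|---|
| 50% (median split) | 0 | 0.3989 | 64% |
| 30% | 0.524 | 0.3477 | 58% |
| 20% | 0.842 | 0.2800 | 49% |
| 10% | 1.282 | 0.1755 | 34% |
| 5% | 1.645 | 0.1031 | 22% |
| 2% | 2.054 | 0.0484 | 12% |

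Worked line for 5%: 0.1031² / (0.05 × 0.95) = 0.01064 / 0.0475 = 0.224. The ratio falls to one half at p ≈ 0.209, so more than half the information is lost only when fewer than about 21% of women are prolonged.

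**4. The same result as power.** With 221 per group, the shift that gives a comparison of means 80% power is (1.960 + 0.842)·√(2/221) = 0.267 SD. For that shift, the comparison of percentages has this power:

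| p in the reference arm | Shift shortens times: p in the other arm, power | Shift lengthens times: p in the other arm, power |
|---|---|---|
| 50% | 39.5%, 60% | 60.5%, 60% |
| 20% | 13.4%, 46% | 28.3%, 53% |
| 10% | 6.1%, 33% | 15.5%, 41% |
| 5% | 2.8%, 22% | 8.4%, 30% |
| 2% | 1.0%, 13% | 3.7%, 19% |

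The benchmark in steps 3 and 4 is the comparison of means under normality. A rank test gives up a little against it, so the gain from the rank test proposed below is slightly smaller than these tables suggest. The size of the shift is chosen only to set the benchmark at 80%; it is not an expected effect.

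**The case against.** The strongest objection is that the choice of test, the cut-off for a derived secondary variable and the handling of manual removal commonly belong in a statistical analysis plan. One may exist that is not shown. That stands for the details: the absence of a test or a number of minutes alone would not be a finding. It does not remove the mismatch, because here the protocol is not silent. It names an outcome in one section, chooses a different quantity in another, and treats its other continuous outcomes differently in the same list.

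A reader might infer that the declared outcome will go unanalysed. The text does not support that. The list is worded as what the main analyses include, not as a complete list; bivariate analyses by arm are also promised; and the percentage prolonged is itself derived from the time, though coarsely.

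A reader might also infer that the percentage throws away most of the information. That holds only below about 21% prolonged. The word suggests a minority in the upper tail, but the protocol gives no prevalence.

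Finally, the shift model favours the continuous comparison. If route acts mainly on delayed placentas, the percentage would not suffer this loss. Nothing in the protocol says which pattern to expect. The percentage is therefore worth keeping, but not as the only listed comparison.

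**Conclusion.** The concern holds in a limited form. Time to placental delivery is declared as an outcome, no comparison of that time is listed, and the one related comparison has no cut-off.

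Under a pure shift in normal or log-normal times, the percentage keeps at most about 64% of the information, and 49%, 34% or 22% at 20%, 10% or 5% prolonged. These figures illustrate the cost of dichotomising. They do not measure a loss in this trial, because the distribution, the shift and the prevalence are all assumed.

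The importance is low. The outcome does not appear in the objectives or research questions, the trial claims no power for it, and neither primary outcome nor the sample size depends on it.

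**What to change.** In Analysis and Dissemination of Results, add as the analysis of this secondary outcome: *time to placental delivery (minutes): median and IQR by arm, compared by a Wilcoxon rank-sum test, with women who have manual removal kept in the analysis and given the worst rank*. The rank-sum test compares the two distributions and is not strictly a test of medians, so the report should describe it that way. With worst ranks, the median and upper quartile remain defined as long as fewer than a quarter of an arm has manual removal.

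Keep the percentage prolonged as a supporting summary, and fix its cut-off in writing before unblinding.

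Confirm that the Randomization/Delivery form has a field for the time of placental delivery, since Study Documentation does not name one. If it does, the cost is one extra line of analysis and no new data. If it does not, the field must be added, because neither the declared outcome nor the percentage can be derived without it.

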**Prophylactic Oxytocin IV Infusion vs. IM Injection in the Third Stage of Labor**

**Research Objectives**

Primary objectives

- To evaluate whether 10 IU prophylactic oxytocin administered in the third stage of labor via IV infusion results in a lower mean blood loss compared to IM injection.
- To also compare the effect of IV infusion and IM oxytocin administration on the proportion of women who experience blood loss  500 ml.

Secondary objectives

- To compare the effect of IV infusion and IM oxytocin administration on the proportion of women who experience blood loss  1000 ml, side effects, adverse events and change in hemoglobin pre- to post-delivery.
- To determine the relationship that exists between changes postpartum in shock index and the severity of bleeding and other PPH outcomes.

This study will provide answers to the following research questions:

1. Is administration of oxytocin by IV infusion more effective than IM administration of oxytocin at reducing post-partum blood loss when provided as part of AMTSL?
2. Is the mean difference between pre-delivery and post-delivery hemoglobin levels less with IV infusion than with IM administration?
3. Do the side effect profiles differ between IV infusion and IM oxytocin administration?

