***Intervention***

Oxytocin 10 IU will be administered either by IV infusion or IM according to randomization assignment as soon as possible after delivery of the baby.

Immediately following delivery of the baby (or last baby, in the case of multiples), blood loss will be measured in a calibrated container for 1 hour. Blood loss will be recorded when active bleeding stops or at 1 hour, whichever is later. In the case of excessive bleeding or PPH requiring treatment, blood loss will be documented also at time of diagnosis. At delivery, some blood can be expected to spatter on the drapes and on the gowns of the attendant, and all attempts will be made to minimize such losses. Additionally, the placental interstices contain maternal blood (about 9% of the placental weight). We expect that overestimations (amniotic fluid) and underestimations (blood loss) are likely to be distributed between the two study arms; therefore there will be no need for corrections to the blood measurement for these inaccuracies.

If a woman experiences excessive bleeding or PPH and requires treatment, she should receive treatment according to standard of care at the study site. If PPH is diagnosed, measurement will continue until the bleeding stops. Health providers can diagnose PPH at any time, but if blood loss reaches 500 ml according to the marking on the calibrated container, PPH should be diagnosed and standard hospital treatment initiated.

The study staff will keep the participants under observation and record all interventions performed during delivery, including the prophylactic oxytocin administration of the study. Also, note if the delivery was induced or stimulated before delivery and if possible, the medication provided, and the time and dose in which it was administered. The provider will be asked to monitor the woman for side effects for 1 hour after delivery. Women will also respond to questions about side effects prior to discharge from the hospital.

In order to document changes in shock index values during the first hour after delivery, the heart rate and blood pressure of all women enrolled at 15, 30, 45 and 60 minute intervals will be recorded. These measurements will be taken independently of the diagnosis of PPH and the exact time of each measurement will be recorded. Automatic devices will be provided to all study centers to measure blood pressure and heart rate in order to standardize such measurements.

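### The analysis section relies on blood loss read at 15, 30, 45 and 60 minutes, but the procedures schedule only pulse and blood pressure at those times

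*Protocol*

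**What the plan says.** The secondary objective is: "To determine the relationship that exists between changes postpartum in shock index and the severity of bleeding and other PPH outcomes". For this purpose, Analysis and Dissemination of Results says that shock index, heart rate and blood pressure will be correlated with "blood loss levels that will be recorded at 15, 30, 45, and 60 minutes following delivery". It also plans to analyse absolute values and changes over the first hour, and to explore associations with other PPH outcomes such as additional interventions and transfusion.

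The procedures describe the data collection differently:

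- **Intervention**, on blood loss: "Blood loss will be recorded when active bleeding stops or at 1 hour, whichever is later". For excessive bleeding or PPH that needs treatment, "blood loss will be documented also at time of diagnosis".
- **Intervention**, on the 15-minute schedule: "the heart rate and blood pressure of all women enrolled at 15, 30, 45 and 60 minute intervals will be recorded". The exact time of each of these measurements is to be noted.
- **Description of Research**: "Blood loss will be measured for 1 hour, and if PPH diagnosed, measurement will continue until cessation of active bleeding". The four-point schedule is again given for pulse and blood pressure only.
- **Outcome Measures**: the first-hour item is "Measurements of blood pressure and pulse during the first hour postpartum". Serial blood loss is not listed.
- **Study Documentation**: the summary of the randomization/delivery form mentions time of delivery, third-stage events and interventions, and any PPH diagnosis. It names no serial volumes.

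**The concern.** The planned correlation needs a blood volume and a set of vital signs from the same woman at the same moment, four times in the first hour. The procedures supply the vital signs at all four times, but a volume only at the end and, for some women, at diagnosis.

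The Background motivates shock index as an aid to early recognition of PPH. One part of that question is how much a woman has lost when her shock index takes a given value. A final volume cannot answer this for a 15-minute reading, because it includes everything lost afterwards and, in treated women, loss after treatment began. A container volume not written down at 15, 30 or 45 minutes cannot be recovered later, so the mismatch has to be resolved before enrolment. An analysis plan written afterwards cannot supply the readings.

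**Working it through.** The protocol gives no figure to reproduce for this point. The check compares what the analysis needs with what the procedures schedule, and then counts readings.

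**Schedule comparison**

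| Time after delivery | Vital signs scheduled | Blood loss needed by the analysis | Blood loss scheduled by the procedures |
|---|---|---|---|
| 15 min | yes | yes | no |
| 30 min | yes | yes | no |
| 45 min | yes | yes | no |
| 60 min | yes | yes | only if active bleeding has stopped by 1 hour |
| End of bleeding, if after 1 hour | no | no | yes |
| PPH diagnosis | no | no | yes, affected women only |

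The 60-minute row follows from the Intervention section. The recording is made at the later of two times, so a woman still bleeding at 1 hour has her volume recorded when bleeding stops. Description of Research, which continues measurement after a PPH diagnosis, does not say that a 1-hour volume is also written down.

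**Count of readings**

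Input: 486 women, 243 per arm (Explanation of Sample Size).

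- Volumes implied by the analysis: 4 × 486 = 1944.
- Volumes scheduled at those times: at most 1 × 486 = 486, and 486 / 1944 = 25%.
- Volumes without a scheduled reading: at least 3 × 486 = 1458, and 1458 / 1944 = 75%.

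The percentages do not depend on the number of women.

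**Readings at diagnosis**

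Inputs: the planning rates of 18% (IM) and 9% (IV infusion) for blood loss of at least 500 ml, from the same section. Assumption: these rates approximate the share of women with a recorded diagnosis.

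- 0.18 × 243 + 0.09 × 243 = 43.7 + 21.9 = 65.6, or about 66 women.

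These readings fall at whatever time the diagnosis is made, so they match a scheduled vital-sign time only by chance. They do not fill the 15-, 30- and 45-minute gaps.

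**The case against.** The strongest reply is that the protocol does not say blood loss is read only at the end. The analysis section states that the interval volumes will be recorded. The Intervention sentence can be read as defining the final volume without excluding earlier readings, and the delivery form, which might have fields for them, is not shown. The clause may also have been meant for the vital signs, which would make this a drafting slip. Part of this stands: absence of the data is not proven, and the finding is an inconsistency between sections. It still needs correcting on either reading. If interval volumes are intended, the procedures omit them; if they are not, the analysis section misdescribes what will be analysed.

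A reader might infer more, and three such inferences are not supported:

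- **That the shock-index objective cannot be met at all.** The objective concerns severity of bleeding and other PPH outcomes and does not itself require time-matched volumes. Shock index at four times, total loss, volume at diagnosis, interventions and transfusion are all collected or listed.
- **That early warning cannot be studied.** A 15-minute shock index can be related to later PPH diagnosis, intervention, transfusion or total loss without a 15-minute volume. The volume recorded at diagnosis also gives a measure of loss around the start of treatment. Only the question of whether shock index tracks concurrent loss needs the interval readings.
- **That a pre-delivery pulse and blood pressure reading is missing.** The protocol promises only postpartum changes within the first hour, and changes from 15 minutes onward meet that wording. The baseline data on Form 1 are not shown either. A pre-delivery reference reading is a matter of preference.

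**Conclusion.** The point holds as an internal contradiction of moderate severity. On the procedures as written, the time-matched correlation cannot be done at 15, 30 and 45 minutes, and at 60 minutes it is not assured for women still bleeding. At least three quarters of the volume readings that the analysis presupposes have no place in the schedule.

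This rests on two assumptions: that sites follow the Description of Research and Intervention sections, and that the delivery form, which is not available, does not already ask for interval volumes. The effect is confined to one analysis under a secondary objective. The rest of that objective, both primary outcomes, the randomised comparison and the sample size are untouched.

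**What to change.** Choose one of two changes before enrolment begins.

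1. **Collect the readings.** Add to Description of Research, to Intervention and to the delivery form: *At each vital-sign time (15, 30, 45 and 60 minutes) the cumulative volume in the calibrated container and the exact time are recorded.* The 60-minute reading is then taken in every woman, including those still bleeding, in addition to the final volume. The cost is three extra readings per woman (1458 in all for 486 women), a separate 60-minute reading for those still bleeding, and a form revision. The container is already in place and staff are already taking vital signs at those times.

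2. **Narrow the analysis.** Reword Analysis and Dissemination of Results so that the interval vital signs are correlated with total blood loss and with loss at diagnosis only, and remove the time-matched claim. This costs one sentence, but the trial then gives up the question of whether shock index follows concurrent loss.

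The first is preferable if that question matters to the sponsor, since the volumes cannot be reconstructed afterwards.
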